## Abstract

Supplemental Digital Content is available in the text

## Introduction

1

Lumbar disc herniation (LDH) results from a pathological change, with lumbar leg pain as the principal symptom, caused by the degeneration of a lumbar intervertebral disc, partial or complete rupture of the annulus fibrosus because of applied external force, outward protrusion of the nucleus pulposus, and cartilage endplate alone or together with stimulation or compression of the nerve root.^[1–3]^ Approximately 9% of the individuals globally have suffered from LDH, and as the population ages, this proportion is likely to increase.^[4]^ The cost of surgical treatment of LDH is approximately 27,000 US dollars, but there are multiple adverse reactions and complications.^[5]^ This factor deters many patients. Clinical experiments^[6–10]^ indicate that acupuncture and Fu's subcutaneous needling (FSN), and especially the latter (Fig. 1) represent the potential treatment for LDH. FSN consists of the needle holder, hose sleeve, and solid stainless steel needle core with sufficient hardness. FSN therapies are a combination of “Traditional Chinese acupuncture medicine” and “modern medicine”. Its therapeutic target is the tender point, namely the myofascial trigger point^[11]^ (MTrP), a key factor that causes pain in more than 93% of patients and the only cause of pain in 85%.^[12,13]^ An FSN therapy is a method of sweeping and dispersing using disposable FSN needles to swing left and right after horizontally inserting the needle around an MTrP or the subcutaneous tissue of adjacent limbs, thus achieving analgesia. The purpose of this study was to explore the feasibility and preliminary results of using floating needle therapy for LDH patients.

**Figure 1 F1:**
[figure not shown]
The difference between FSN and acupuncture. (A) Undismantled FSN and acupuncture (right 1). (B) Demolition of FSN and acupuncture (right 1). FSN = Fu's subcutaneous needling.

## Methods

2

### Study design

2.1

The present study is a single-blind, randomized controlled clinical study that applies the ethical principles of China's Ministry of Health's “Ethical Review Measures for Biomedical Research Involving Human Beings (Trial 2007)”, “Regulations on Clinical Trials of Medical Devices (2004)”, WMA's “Helsinki Declaration”, and CIOMS's “International Ethical Guidelines for Biomedical Research on Human Beings”. The project was evaluated and approved by the Research Ethics Committee of Gansu Provincial Hospital of Traditional Chinese Medicine (Ethical batch No. FJ/01-IRB/C/018-V3.0, Ethics Review Adoption Form places in the Supplemental Digital Content). The protocols were first released and last updated in June 2019. Treatment will be conducted in Gansu Provincial Hospital of Traditional Chinese Medicine from January 1, 2020 to June 30, 2020. The schedule of pre-intervention, intervention, and evaluation procedures will be presented in Supplemental material 1. A flow chart representing the stages of this study is shown in Supplemental material 2.

### Participants

2.2

The following eligibility criteria apply to all patients for recruitment into the study. Patients will be recruited through the acupuncture clinic of Gansu Provincial Hospital of Traditional Chinese Medicine. After oral explanation and reading of the procedures used in the study, patients agreeing to participate will sign an informed consent form.

Inclusion criteria:

Aged between 20 and 75 years;Fulfilling the diagnostic criteria for LDH published by the North American Spinal Surgery Association^[14]^ in 2013 (manual muscle testing, sensory testing, supine straight leg raise test, Lasegue sign and crossed Lasegue sign are all considered diagnosable);Those unconcerned about FSN or acupuncture treatment;Willing to enter the clinical trial and provide signed informed consent.

Exclusion criteria:

Compression fracture or tuberculosis found at the lesion site;Horsetail nerve damage syndrome leading to saddle paralysis, defecation, weakness of micturition, urinary retention and urinary incontinence, and absolute surgical indications;Skin infection, ulcers, scars, or tumors that cannot be punctured;Coagulation dysfunction;Severe arrhythmia, heart failure, chronic obstructive pulmonary disease, an endocrine disease, epilepsy, or mental illness;Patients with infectious diseases, acute inflammation, fever, or pregnant women;Combined medication or participation in other trials during treatment.

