#### FSN group

2.3.1

*FSN selection*: Disposable floating needles (medium: M) produced by Nanjing Paifu Medical Science and Technology Co., Ltd. were selected for use in this trial. These have passed inspection and have obtained a production license (License no: su Shi Yao Jian Xie Xu 20040104; Registration no: 20152270832).

*Procedure*: The patient is placed in a prone position and the MTrP P1, P2, P3, and P4 ascertained (the four positions determined according to positions causing pain, where P1 and P2 points are at the waist, P3 points at the thigh and P4 points on the calf). The position of needle insertion is 3 to 5 cm below or outside the MTrP. An FSN needle insertion device is required to insert the needle. Insertion of the needle tip is required to be at an oblique angle of 15° to 20° relative to the surface of the skin. The preferable insertion depth of the needle is just beyond the depth of the subcutaneous muscle layer. The thumb, index finger, and middle finger are used to move the upper part of the needle body, lift and pinch the needle handle, and sense the tightness of the muscle as the needle tip moves in response to movement of the fingers. The needle body is then gently and slowly lifted until the needle tip leaves the muscle layer and enters the subcutaneous layer for additional sweeping treatment. The duration of scanning time at each needle entry point is approximately 2 minutes, each position scanned approximately 200 times. The treatment cycle requires 3 weeks, usually once a day for the first 3 days, then 2 days apart, for a total of 12 occasions.

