### Discontinuation criteria

2.7

Any serious adverse reactions or other acute or severe event during the study, preventing continued participation in the study;Subjects requesting to withdraw from the study midway;Patients not cooperating with the treatment plan, preventing valid treatment execution even after repeated explanation by the clinician.Results of those exceeding half of the total course of treatment available for inclusion in the statistical analysis of treatments.

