##### VAS^[16]^

2.8.1.1

Patients were marked on a 100-mm visual analogue scale prior to and 3 weeks following treatment for assessment of their pain level (from no pain to very severe), which was then recorded by the evaluator.

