### Statistical analysis

2.11

Since FSN and acupuncture are known to have only minimal risk, implementation of additional safety precautions is not required. Sensitivity analysis will be conducted to determine the impact of incomplete records on the results. Missing data will not be estimated. Statistical analysis will be performed using R package v3.4.4 software. If a Shapiro–Wilk test indicates that the data are normally distributed, a *t* test is appropriate for calculation and comparison of differences between two groups, otherwise a Mann–Whitney *U* test is suitable. A *χ*^2^ or Fisher exact test is relevant for calculation of differences in count data.

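### An exclusion criterion turns on medication or other-trial participation during the treatment period; applied as worded after randomisation, it could drop patients in an outcome-related way, and it does not fit section 2.7

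*Protocol article*

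**What the plan says.** All references are to the protocol article.

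- **Section 2.2, Participants.** The eligibility list opens with its scope: "The following eligibility criteria apply to all patients for recruitment into the study". Its last exclusion item is "Combined medication or participation in other trials during treatment". No drug class, time window or washout is given.
- **Section 2.3.1, FSN group.** The period in question is the treatment course: "The treatment cycle requires 3 weeks, usually once a day for the first 3 days, then 2 days apart, for a total of 12 occasions". Section 2.3.2 gives the acupuncture group the same length and number of sessions.
- **Section 2.7, Discontinuation criteria.** Medication is not named. The nearest item is "Patients not cooperating with the treatment plan, preventing valid treatment execution". The last item concerns the analysis: "Results of those exceeding half of the total course of treatment available for inclusion in the statistical analysis of treatments".
- **Section 2.11, Statistical analysis.** "Missing data will not be estimated", and "Sensitivity analysis will be conducted to determine the impact of incomplete records on the results". Neither sentence mentions medication use.
- **Section 2.8.1.1, VAS.** Pain is a primary outcome: "Patients were marked on a 100-mm visual analogue scale prior to and 3 weeks following treatment".

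The article does not state that all randomised patients are analysed in their allocated group.

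**The concern.** An eligibility criterion has to be decidable before allocation. Whether a patient takes other medication, or joins another trial, in the coming 3 weeks is not known at that point. Read literally, the item can only be triggered after randomisation.

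In a pain trial that matters, because medication use may be a consequence of the allocated treatment. The Discussion itself describes opioids and anti-inflammatory drugs as being used for back and leg pain, which is the symptom the VAS measures. It is reasonable to suppose, though the article gives no data on it, that patients with less relief take more. If such patients were dropped, the remaining groups would no longer be those formed by randomisation.

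The article does not say who would apply the criterion. The practitioners open the envelopes (section 2.5) and so know the allocation, which leaves room for uneven application.

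**Working it through.** **1. The sections side by side.** Take a patient who is randomised, receives 7 of the 12 sessions (more than half of 12, which is 6) and takes another drug in week 2.

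| Section | Treatment of this patient |
|---|---|
| 2.2, literal reading | Meets an exclusion criterion |
| 2.2, read as a recruitment screen | Was eligible at entry; nothing said about later use |
| 2.7, discontinuation items | Not named; non-cooperation applies only if it prevents valid treatment |
| 2.7, last item | Results available for analysis, no medication condition |
| 2.11 | No rule; the sensitivity analysis concerns incomplete records |

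The literal reading of 2.2 and the last item of 2.7 give opposite answers. The recruitment reading removes the conflict, but it is not what the words of the item say. The only rule on inclusion in the analysis that the article shows (2.7) also depends on what happens after randomisation.

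**2. Size, simple form.** The plan has no figure of its own on this point to reproduce. All inputs below are assumptions.

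Let *p* be the share of users in an arm, *g* the amount by which users' final VAS exceeds that of non-users, and *m* the mean in non-users. The mean of the whole arm is *m + p·g*, and after users are removed it is *m*. Removal therefore lowers the arm mean by *p·g*. With the same *g* in both arms, the difference (worse arm minus better arm) shrinks by (*p*₁ − *p*₂)·*g*, where *p*₁ is the share in the worse arm.

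With *g* = 20 mm:

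- 15% v 5%: (0.15 − 0.05) × 20 = 2 mm smaller.
- 15% v 0%: 0.15 × 20 = 3 mm smaller.
- 15% v 15%: 0 mm.
- 5% in the worse arm v 15% in the better: (0.05 − 0.15) × 20 = −2 mm, so the difference widens by 2 mm.
- *g* = 0: 0 mm whatever the shares.

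At 40 per arm (80 patients, 1:1), 15% and 5% are 6 and 2 patients, leaving 80 − 8 = 72.

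**3. Size, by simulation.** Assumptions: final VAS normal with SD 20 mm; acupuncture mean 35 mm; FSN mean 35 or 25 mm; medication use driven by a latent variable correlated 0, 0.5 or 0.9 with final VAS; 10% or 25% users in the acupuncture arm; all users removed; one million patients per arm.

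| True difference | Correlation | Removed, acupuncture v FSN | Observed difference |
|---|---|---|---|
| 10 mm | 0 | 10% v 10%; 25% v 25% | about 10 mm |
| 10 mm | 0.5 | 10% v 6.3% | 9.4 mm |
| 10 mm | 0.5 | 25% v 17.7% | 8.9 mm |
| 10 mm | 0.9 | 10% v 4.2% | 8.2 mm |
| 10 mm | 0.9 | 25% v 13.0% | 6.8 mm |
| 0 mm | 0.5 or 0.9 | equal in both arms | about 0 mm |

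In the last row each arm's mean still looks 1.9 to 7.6 mm better than it was, but equally so in both.

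**4. Scale.** For 80% power at two-sided .05 (the article does not state sidedness), the detectable difference is (1.96 + 0.842) × √(1/*n*₁ + 1/*n*₂) × SD. With the assumed SD of 20 mm this is 0.626 × 20 = 12.5 mm for 40 + 40, and 0.725 × 20 = 14.5 mm for the 32 + 28 of section 2.4. A shift of 2 mm is about 14% to 16% of that (2/14.5 to 2/12.5).

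**The case against.** A reader might infer that randomised patients who take medication are declared ineligible, and that the plan thereby removes poor responders. The documents do not support that. The list is introduced as a recruitment screen, and the item can be read as asking about current or planned medication or trial participation, which can be established at entry. No section orders removal of a medication user.

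Nor does it follow, because section 2.7 omits medication, that exclusion is the only handling the plan offers. Its last item makes results past half of the course available without a medication condition, and non-cooperation could at most be stretched to cover some users.

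Three further points have force. The criterion names no drug class and also covers other-trial participation, which has no evident link to response. The rates, the gap and the SD are all assumed. In the simulated model no false benefit appears: the bias is zero with no true difference and toward no difference otherwise. It is also true that if users are more frequent in the weaker arm and the drug works, keeping them in the analysis narrows the observed difference too. The gain from keeping them is that the comparison remains between the randomised groups; it is not a larger effect.

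Finally, a journal article leaves much of the handling of concomitant medication to documents not shown. That disposes of any complaint about missing detail. It does not dispose of a stated criterion whose wording conflicts with its stated scope and with section 2.7.

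**Conclusion.** The point stands in a conditional form. The criterion is misplaced as worded: it depends on the treatment period while the list applies at recruitment, and its literal reading contradicts section 2.7. Following it literally after randomisation could drop patients in an outcome-related way.

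The consequence is possible, not established. With a similar gap between users and non-users in both arms, it requires that medication use be related to outcome and differ between arms. Under 15% v 5% users, the larger share in the arm that does worse, and a 20 mm gap, the shift is about 2 mm toward no difference. In the simulation a true 10 mm difference falls to between 9.4 and 6.8 mm. None of these inputs comes from the article. This is worth correcting because the correction is cheap, but on these figures it would not decide the trial by itself.

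**What to change.** - In section 2.2, reword the item to what can be established at screening: current or planned medication, and current or planned participation in another trial.
- Reconcile sections 2.2 and 2.7, so that a patient who starts medication after randomisation is treated the same way in both.
- State that medication use or other-trial participation after randomisation is recorded, up to the final assessment, and does not remove the patient from the main analysis, which compares the groups as randomised.
- Report such use by arm. Keep exclusion of users only as a secondary or sensitivity analysis.

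The cost is one reworded line, a short statement on the analysis, one case report form field and one table. The downside is that the main comparison then includes any effect of the medication, which should be said when the result is interpreted. Which medication is permitted is a clinical matter and is not addressed here.

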### Study interventions

2.3

#### FSN group

2.3.1

*FSN selection*: Disposable floating needles (medium: M) produced by Nanjing Paifu Medical Science and Technology Co., Ltd. were selected for use in this trial. These have passed inspection and have obtained a production license (License no: su Shi Yao Jian Xie Xu 20040104; Registration no: 20152270832).

*Procedure*: The patient is placed in a prone position and the MTrP P1, P2, P3, and P4 ascertained (the four positions determined according to positions causing pain, where P1 and P2 points are at the waist, P3 points at the thigh and P4 points on the calf). The position of needle insertion is 3 to 5 cm below or outside the MTrP. An FSN needle insertion device is required to insert the needle. Insertion of the needle tip is required to be at an oblique angle of 15° to 20° relative to the surface of the skin. The preferable insertion depth of the needle is just beyond the depth of the subcutaneous muscle layer. The thumb, index finger, and middle finger are used to move the upper part of the needle body, lift and pinch the needle handle, and sense the tightness of the muscle as the needle tip moves in response to movement of the fingers. The needle body is then gently and slowly lifted until the needle tip leaves the muscle layer and enters the subcutaneous layer for additional sweeping treatment. The duration of scanning time at each needle entry point is approximately 2 minutes, each position scanned approximately 200 times. The treatment cycle requires 3 weeks, usually once a day for the first 3 days, then 2 days apart, for a total of 12 occasions.

#### Acupuncture group

2.3.2

*Acupuncture needle selection*: Jiajian brand disposable sterile Acupuncture needles, 0.30 × 40 mm and 0.30 × 75 mm, with a production license no: 20060095. *Procedure*: Acupuncture of the bilateral Shenshu (BL 23), Jiaji (BX-B2), Weizhong (BL 40), and Ashi acupuncture points (irregular). The treatment cycle selected for this study was 3 weeks, usually once per day for the first 3 days, then 2 days apart, for a total of 12 occasions.

### Sample size calculation

2.4

In order to determine the number of participants required for each experimental group, the variability of results in a previously published article^[7]^ was used in the calculation. The main results of the two studies were obtained under similar circumstances. The sample size required for an unpaired *t* test was 60 individuals, including 32 in the FSN group and 28 in the acupuncture group. The calculation was performed using a significance level of .05 (i.e., 5% of type I errors, resulting in a 95% confidence interval) and an absolute error of 5%. Considering a dropout rate of 10%, 80 patients are required to generate 80% of the power, at a significance level of .05.^[15]^

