### Randomization and allocation concealment

2.5

In the present study, the 80 recruited patients were divided into FSN and acupuncture groups at a ratio of 1:1. A statistical expert not involved in the design of the study used R Package v3.4.4 to generate a set of random sequences, to be sealed in opaque envelopes prepared in advance. Only FSN and acupuncture practitioners were authorized to open the envelopes to obtain each grouping code.

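### Section 2.4: 60 patients with 10% dropout gives 67 (68 at 1:1, at most 72), not 80, so the step to 80 and its 80% power are unsupported

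*Protocol article*

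**What the plan says.** Section 2.4 (Sample size calculation) takes "the variability of results in a previously published article" as its basis and says that an unpaired t test needs "60 individuals, including 32 in the FSN group and 28 in the acupuncture group". On the error rates it says "The calculation was performed using a significance level of .05", which it glosses as "5% of type I errors, resulting in a 95% confidence interval", and it adds "an absolute error of 5" percent. It closes with "Considering a dropout rate of 10%, 80 patients are required to generate 80% of the power", again at the .05 level. Power is mentioned only in that closing sentence, where it is attached to the 80.

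Section 2.5 (Randomization and allocation concealment) says that "the 80 recruited patients were divided into FSN and acupuncture groups at a ratio of 1:1", which is 40 per arm.

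Section 2.4 prints no difference to detect and no standard deviation (SD). It does not say which of the three primary outcomes in Section 2.8.1 (VAS, JOA score, ODI) was used.

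**The concern.** The paragraph reads as a chain: a t test requirement of 60, a 10% dropout allowance, a total of 80. The last step fails by simple division. Two other parts of the paragraph add to the doubt. An absolute error is what one specifies to estimate a single quantity to a given precision; a two-sample t test is sized from a difference, an SD, a significance level and a power. And a calculation with equal variances for 1:1 allocation returns equal arms, not 32 and 28.

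What is at stake is the justification for the trial's size. A reader cannot tell whether the evaluable requirement is 60 or the 72 that remain after 10% loss from 80. The two answers imply different target effects and different power.

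**Working it through.** **Inputs.** From Section 2.4: evaluable requirement 60 (32 + 28), dropout 10%, significance level .05, total 80, power 80%. From Section 2.5: 1:1 allocation. Two-sidedness is an assumption; the text does not state it, but the reference to a 95% confidence interval suggests it.

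**Can the 60 be reproduced?** No. No difference or SD is printed, so the check starts from the 60 as given.

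**Can the 80 be reproduced from 60 and 10%?** The standard formula is N = n / (1 − dropout).

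| Reading | Arithmetic | Total |
|---|---|---|
| Inflate the total | 60 / 0.90 = 66.7 | 67 |
| Same at 1:1 | 30 / 0.90 = 33.3, so 34 per arm | 68 |
| Arm by arm | 32 / 0.90 = 35.6, so 36; 28 / 0.90 = 31.1, so 32 | 68 |
| Larger arm kept in both groups | 2 × 36 | 72 |
| Multiplying instead of dividing | 60 × 1.10 | 66 |
| 10% loss applied twice | 60 / 0.90 / 0.90 = 74.1 | 75 |

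None gives 80. The gap from 67 is 13 patients (13 / 67 = 19%), and from the most generous single-step reading it is 80 − 72 = 8. Rounding does not explain either.

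**What dropout would give 80?** From 60: 1 − 60/80 = 25%. From 2 × 32 = 64: 1 − 64/80 = 20%. Neither is the stated 10%.

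**What does this do to power?** At 10% loss, 80 × 0.90 = 72 evaluable, or 36 per arm. Power comes from the noncentral t distribution with n₁ + n₂ − 2 degrees of freedom and noncentrality d / √(1/n₁ + 1/n₂), where d is the difference divided by the SD.

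- For 32/28: √(1/32 + 1/28) = 0.259. For 36/36: √(2/36) = 0.236.
- *If 60 is the 80%-power requirement:* 32/28 has 80% power at d = 0.737. At that d, 36/36 has noncentrality 0.737 / 0.236 = 3.1 and power 0.870.
- *If 36/36 is the 80%-power requirement:* d = 0.670. At that d, 32/28 has noncentrality 0.670 / 0.259 = 2.6 and power 0.721.

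**Does the 32/28 split matter for power?** Hardly. At d = 0.737, 30/30 has power 0.802 against 0.800 for 32/28. The split is a question about how the calculation was done, not about lost power.

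**The case against.** The strongest reply is that the error is harmless. Eighty exceeds every total that 60 and 10% can yield, and 40 per arm less 10% leaves 36, which covers both the 32 and the 28. The Introduction also describes the aim as exploring feasibility and preliminary results. The first part stands whenever 60 is the true requirement. It does not settle the matter, because the text attaches the 80% power to the 80, and on that reading 60 is not enough.

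Four stronger readings are tempting, and the document does not support them.

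- *That the trial is underpowered.* Nothing shows this; if 60 is the requirement, the plan is conservative.
- *That the stated dropout, size and power cannot all be true.* Section 2.4 gives no power for the 60. Eighty randomised, 10% loss and 80% power are jointly possible (36/36, d about 0.67). What fails is the derivation of 80 from 60.
- *That 32/28 contradicts the 1:1 allocation.* The 32/28 is an intermediate planning figure, while Section 2.5 governs the 80 who are randomised. Unequal SDs in the two arms of the cited study could explain it. It is unexplained, not contradictory.
- *That a non-significant result could not be interpreted.* It can be read from the estimate and its confidence interval, whatever the planning paragraph says.

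It is also fair to say that the outcome, difference and SD may stand in the full protocol, which is not shown. Their absence from an article is not the point here. They are needed only because the printed figures do not agree and have to be reconciled.

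**Conclusion.** The point holds as a derivation error. The printed 60 and 10% give 67, or 68 at 1:1, or 72 if both arms keep 32. They do not give 80, which would need 25% loss from 60 or 20% from 64. The 5% absolute error is not an input to t-test power, and the 32/28 split is unexplained. The 80% power is therefore unsupported, which is a weaker statement than saying it is wrong.

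The power consequence depends on which number is the requirement: about 87% at 10% loss if it is 60, or about 72% for 60 evaluable if it is 72. Both figures assume a two-sided .05 t test with equal variances and a single effect size. The dropout arithmetic needs none of these assumptions.

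**What to change.** Keep 80 patients and restate Section 2.4 from the calculation that was actually performed, rather than choosing a rationale that happens to fit 80:

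- Name the outcome, and give the difference and SD used and whether the test is two-sided.
- Give one evaluable number per arm at 1:1. If 32 and 28 came from unequal SDs, say so and state how they became equal arms.
- Apply dropout as n / (1 − dropout).
- Correct whichever of the 60, the 10% or the 80% power is wrong, so that all of them agree with 80.
- Remove the 5% absolute error unless it truly was an input; if it was, say what it refers to.

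The cost is one rewritten paragraph. No patients are added, and neither the allocation nor the analysis changes.
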